# Transcutaneous Electrical Cranial-Auricular Acupoint Stimulation vs. Escitalopram for Patients With Mild-to-Moderate Depression (TECAS): Study Design for a Randomized Controlled, Non-inferiority Trial

**DOI:** 10.3389/fpsyt.2022.829932

**Published:** 2022-05-10

**Keywords:** depression, transcutaneous electrical cranial-auricular acupoint stimulation, escitalopram, non-inferiority, randomized controlled trial

## Abstract

**Background:**

Previous studies in animals and humans indicated that transcutaneous vagus nerve stimulation (tVNS) and transcutaneous electrical acupoint stimulation (TEAS) on trigeminal nerve-innervated forehead acupoints can relief the symptoms of depression. However, due to the limited investigations on these two interventions, more research are needed to confirm their efficacy in depression. To improve the efficacy of the single treatment, we combined two treatments and created a novel non-invasive stimulation, transcutaneous electrical cranial-auricular acupoint stimulation (TECAS). To assess the efficacy and safety of TECAS, we compare it with a selective serotonin reuptake inhibitor (SSRI), escitalopram, for the treatment of depression.

**Methods/Design:**

This is a multi-center, non-inferiority, randomized controlled trial that will involve 470 patients with mild to moderate depression. Patients will be randomly assigned to either the TECAS group or the escitalopram group in a 1:1 ratio. The TEAS group will receive two sessions of treatments per day for 8 consecutive weeks, and the escitalopram group will receive 8 weeks of oral escitalopram tablets prescribed by clinical psychiatrists as appropriate for their condition. The primary outcome is the clinical response as determined by Montgomery-Åsberg Depression Rating Scale (MADRS) scores at week 8, with −10% as the non-inferior margin. The secondary outcomes include the response rate determined by 17-item Hamilton Depression Rating Scale (HAMD-17), remission rate, changes from baseline in the scores on the MADRS, the HAMD-17, the Hamilton Anxiety Rating Scale (HAMA), the Pittsburgh Sleep Quality Index (PSQI), and the Short Form 36 Health Survey (SF-36).

**Discussion:**

This will be the first randomized controlled trial to compare the efficacy of TECAS with escitalopram for depression. If effective, this novel intervention could have significant clinical and research implications for patients with depression.

**Clinical Trial Registration:**

[ClinicalTrials.gov], identifier [NCT03909217].

## Introduction

Major depressive disorder (MDD) is highly prevalent worldwide, representing a significant global burden (1). Currently, second generation agents including antidepressants such as selective serotonin reuptake inhibitors (SSRIs) and serotonin and norepinephrine reuptake inhibitors (SNRIs) are commonly recommended as a first-line treatment option for depression (2–4). However, attributed to the neurological and gastrointestinal adverse effects, the adherence to antidepressants were low, with nearly half no longer refilling their first prescription (5).

Brain stimulation techniques are increasingly used for treatment-resistant depression (6). Among them, vagus nerve stimulation (VNS) uses electrical stimulation to provides chronic bilateral activation of brain circuits (7). Long-term VNS has been demonstrated to be correlated to sustainable patient benefits (8–11). In 2005, the US FDA has approved VNS for managing treatment-resistant depression. To date, more than 100,000 patients with psychiatric or neurological indications are treated with VNS each year (12). Conventional implantable VNS (iVNS) requires a surgical implantation procedure, which restricts its accessibility and increases the financial costs and complications, such as voice changes, bradycardia, dyspnea, cough and pain (2, 13). To alleviate these barriers arising from the invasive process and to improve the tolerability and practicability of VNS, transcutaneous VNS (tVNS) has been developed. Different from iVNS modalities, transcutaneous VNS (tVNS) uses electrodes placed on the skin surface to produce electrical stimulation to the auricular branch or cervical branch of the vagus nerve. The available evidence suggests tVNS’s effects in alleviating depressive symptoms (14, 15). However, depression guidelines and systematic reviews consider VNS more as an adjunct therapeutic method to existing primary treatments (2, 3, 8, 13). The effectiveness of its short-term treatment remains controversial (16–18). A randomized controlled trial with 235 treatment-resistant depression patients failed to show a significant advantage of short-term VNS therapy over placebo (17). Therefore, we expect to involve additional neurostimulation to enhance the effectiveness of VNS in the treatment of depression.

Previous studies in animals and humans and our pilot study (unpublished data) have shown that electrical acupuncture in the cranial region can improve symptoms of depression (19–26). Similarly, the Evidence-based Guidelines of Clinical Practice with Acupuncture and Moxibustion–Depression (Revised) recommends the cranial acupoints Yin-Tang (EX-HN3) and Bai-Hui (DU20) for depression (27). Those forehead acupoints are found innervated by the trigeminal nerve (28), while the stimulation process activates the sensory pathways of the trigeminal nerve (29). However, as an invasive treatment, electro-acupuncture is prone to clinical side effects such as infection, needling pain, and subcutaneous hematoma. In addition, an experienced acupuncturist is required to perform the treatment. All these reasons reduced adherence as well as cost-effectiveness of acupuncture treatment (30). Therefore, a novel method for acupoints stimulation called transcutaneous electrical acupoint stimulation (TEAS) was developed. It is easy-to-use and non-invasive, which increases safety by avoiding the process of needling and the resulting side effects of pain and needle phobia (31). Although more clinical evidence on cranial TEAS for depression is still needed, results of a 8-week open pilot study including 11 patients with moderate to severe depression and taking concurrent antidepressant medication suggested that nightly transcutaneous trigeminal nerve stimulation (V1 branch) can significantly improve the depressive symptoms assessed by clinician-rated or self-rated scales (32). Moreover, Shiozawa’s team conducted a phase II, randomized, sham-controlled trial of 40 patients with MDD to test the effects of a 10-day stimulation of the supraorbital branches of the trigeminal nerve while taking concurrent antidepressant medication. The results showed that although there was a significant interaction for changes in depressive symptoms over treatment and control groups across three assessments; *post-hoc* analyses found significant differences between depressive symptoms at baseline and after intervention protocol, as well as between at baseline and during 1-month follow-up (33). These evidence suggests the possible efficacy of using transcutaneous acupoint trigeminal nerve stimulation for depression. As TEAS and tVNS are both safe and practical methods producing stimulation with similar principles and equipment requirements, combining the two does not place an additional burden on patients. Therefore, we combined transcutaneous electrical stimulation of the Yin-tang and Bai-hui acupoints with tVNS to create a novel electrical stimulation method called transcutaneous electrical cranial-auricular acupoint stimulation (TECAS). In addition to the stimulation of the vagus nerve provided by tVNS, this new method involves TEAS stimulation of the trigeminal nerve through the relevant acupoints. We expect that the addition of this transcranial trigeminal nerve stimulation could be additive to the effectiveness of the original auricular vagus nerve stimulation for depression.

To evaluate the efficacy and safety of TECAS in improving depressive symptoms, accompanying anxiety, insomnia, and the quality of life for patients with mild-to-moderate depression, we designed a randomized controlled trial with non-inferiority design comparing the efficacy of TECAS and a commonly used, representative SSRI, escitalopram. The results of this study will provide robust evidence on whether TECAS has the potential to become a safe and effective treatment for depression.

## Methods and Analysis

### Design

The TECAS trial is a multi-center, non-inferiority, randomized controlled trial and will be conducted simultaneously at five hospitals in China including The University of Hong Kong-Shenzhen Hospital; Guang’anmen Hospital of China Academy of Chinese Medical Sciences; Beijing First Hospital of integrated Chinese and Western Medicine; The First Hospital of Hebei Medical University; and Southwest Medical University, Hospital of Traditional Chinese Medicine. This study protocol is developed according to the Standard Protocol Items: Recommendations for Intervention Trials (SPIRIT) checklist (34) and has been approved by the Research Ethical Committee of The University of Hong Kong Shenzhen Hospital (HKU-SZH) (project approval number: 2019044; approved on 28 February, 2019), and all participating medical sites. The study protocol has been previously registered at ClinicalTrials.gov (NCT03909217). Figure 1 presents a study flow chart of the progress of patients through the trial.

**FIGURE 1 F1:**
[figure not shown]
Study flow chart.

### Participants

Four hundred and seventy patients with mild-to-moderate depression will be recruited *via* hospitals, posters, and web advertisements. Participants will be recruited after referral to specialty psychiatrists at five hospitals. We will recruit adults aged 18–70 years who have a confirmed diagnosis based on the International Classification of Diseases 10th Edition (ICD-10, F32) of mild-to-moderate depression. A patient will be eligible if their current episode shows a Montgomery-Åsberg Depression Rating Scale (MADRS) score of at least 12 and less than 30; and all responses to the Suicide Severity Scale (C-SSRS) were “no” or scored <3 points. The exclusion criteria including the patients with severe diseases of heart, brain, liver, kidney or hematopoietic system, with acute diseases, infectious diseases or malignant tumors; with any history of psychosis or mania; with cognitive disorders or personality disorders; with serious suicidal ideation or behaviors; the patients who unable to stop taking relevant drugs according to the treatment requirements, or pregnant. Professional psychiatrists will be responsible for the assessment of the mentioned disorders in exclusion criteria based on the appropriate clinical diagnostic criteria in China. Participants were prohibited to use any other drug or non-pharmacological therapy, including phytomedicine, antidepressants, and physical therapy methods or ways, which may affect the depression symptoms during the treatment period. All participants have to provide written, informed consent.

### Randomization

Patients will be randomly allocated (1:1) to groups receiving either escitalopram or TECAS. Stratified blocked randomization codes will be generated by PROC PLAN using SAS software, which will be stratified by the study site. The research assistants will use the randomization codes to produce opaque, sealed envelopes. Each envelope will be labeled with a participant-specific randomization identification number and contain a treatment allocation number. After the collection of patients’ basic information, participants will be assigned a randomization identification number by study staff. By using a central randomization system composed of free telephone, short message, and E-mail, the randomization identification number and treatment allocation will be accessed after participants received their baseline clinical evaluation. Participants, clinical psychiatrists, and treatment technicians will be aware of the treatment condition. The staff assessing treatment outcomes will be blinded to treatment condition because they will be segregated in a different clinic area. The participants’ treatment allocation will be required not to be discussed with these staff or other participants.

### Intervention Procedure

Before receiving interventions, participants will receive related detection including blood routine, urine routine and electrocardiogram, or to provide the results of a physical examination within 2 weeks. The TECAS treatment consisted of two sessions per day for 8 consecutive weeks. For patients who will receive TECAS treatment, cranial Yin-Tang (EX-HN3), Bai-Hui (GV20) acupoints electrical stimulation and auricular vagus nerve electrical stimulation will be used. The patients will take a supine position or sitting position and will use the SDZ-IIB (Hwato, Jiangsu) electronic acupuncture instrument equipped with two pairs of cranial and auricular electrodes. The cranial electrodes will be located in EX-HN3 and GV20 acupoints, and the auricular electrodes will be located in the bilateral distribution area of the vagus nerve of the cavity and cymba of the auricular concha (Figure 2). The cranial and auricular electrodes stimulation will last for 30 min each session with a disperse-dense wave. This duration has been applied in several previous related electrical stimulation experiments, whose results suggest its efficacy and safety (19, 33, 35). Previous study on electroacupuncture indicated that low frequency could produce broader neuromodulation compared to higher frequency (36). Also, due to safety considerations, vagus nerve stimulation is conventionally constrained to administration at fairly low frequencies (≤30 Hz) (37). Considering the above literature and our clinical experience, the frequency will be adjusted to 4/20 Hz (4 Hz for 5 s, 20 Hz for 10 s, alternately). The intensity will be adjusted to be tolerable without pain. Patients will be treated at home twice a day as required, once in the morning and once in the evening (the evening treatment could be done 30 min before bedtime). Prior to the start of home treatment, the study team will hold a training session for participants to ensure that they are familiar with the precautions for using the device.

**FIGURE 2 F2:**
[figure not shown]
Illustration of Transcutaneous electrical cranial-auricular acupoint stimulation (TECAS).

For patients who will receive escitalopram treatment, oral administration escitalopram tablets will be prescribed by clinical psychiatrists with respect to patients’ conditions for 8 consecutive weeks. The usual dosage is 5 mg daily in the first week and 10 mg daily from the second week. Clinicians can increase the maximum daily dose to 20 mg daily depending on the patient’s response, condition, and course of the disease. For elderly patients (>65 years of age), it is recommended to start the treatment at half of the usual starting dose described above, and the maximum dose should be reduced accordingly.

In terms of the drug combination, for patients with severe insomnia, the treatment group and control group can be combined with weak diazepam or non-benzodiazepine sedative drugs; the drug use should be recorded in the case report form (CRF). The MADRS score, the 17-item Hamilton Depression Rating Scale (HAMD-17) score, the Hamilton Anxiety Rating Scale (HAMA) score, the Pittsburgh Sleep Quality Index (PSQI) score and the Short Form 36 Health Survey (SF-36) will be assessed by trained research assistants at baseline, 2, 4, 8, and 12 weeks. Adverse events (AE) of all participants will be assessed and evaluated during the whole procedure, as well as laboratory tests (blood routine, urine routine, and electrocardiogram) if needed.

### Outcomes

#### Primary Outcome

The primary outcome is clinical response at the end of treatment. The responder is defined as a ≥50% reduction from baseline MADRS at week 8. MADRS is a validated, self-reported and well-recognized questionnaire for depression (38–40). It consists of nine items, with the total range of 0–60 (higher scores indicate more severe condition). Previous research estimated the minimal clinically important difference (MCID) of MADRS to be 1.6–1.9 points changed from baseline (41).

#### Secondary Outcomes

The secondary outcomes include (a) response rate based on HAMD-17. The responder is defined as the rate of a ≥50% reduction from baseline HAMD-17 at week 8; (b) remission rate, which is defined as a score of 12 or fewer points on the MADRS or as 7 or fewer points on the HAMD-17 at the end of treatment; (c) changes from baseline in the MADRS at week 2, 4, 8, and 12; (d) changes from baseline in the HAMA at week 2, 4, 8, and 12; (e) changes from baseline in the PSQI at week 2, 4, 8, and 12; (f) changes from baseline in the SF-36 at week 2, 4, 8, and 12; (g) changes from baseline in the HAMD-17 at week 2, 4, 8, and 12. HAMD-17 is a validated questionnaire that needs to be assessed by clinicians (42). The range of HAMD-17 is 0–52 (higher scores indicate more severe condition). HAMA is a validated 14-item scale for the measurements of psychic anxiety and somatic anxiety (43). Each item of HAMA ranges from 0 to 4, with a total range of 0–56. PSQI consists of 19 items, and is a reliable self-reported questionnaire for the measurement of sleep dysfunction (higher scores indicate more severe condition) (44). SF-36 is made up of 36 items grouped in 8 dimensions (45). This scale is used to assess the overall health status of patients. Figure 3 illustrates the SPIRIT diagram of assessments at enrollment, allocation, and different time points.

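### The MADRS remission cut-off overlaps the entry range, so a patient can count as remitted with little or no improvement, and at 12 of the 18 admissible baseline scores remission needs a smaller fall than response

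*Protocol article*

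**What the plan says.** Four statements in the protocol article bear on this point.

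- **Entry (Participants):** the current episode must show a "Montgomery-Åsberg Depression Rating Scale (MADRS) score of at least 12 and less than 30". No minimum HAMD-17 score is given.
- **Response (Primary Outcome):** "The responder is defined as a ≥50% reduction from baseline MADRS at week 8".
- **Remission (Secondary Outcomes, item b):** "defined as a score of 12 or fewer points on the MADRS or as 7 or fewer points on the HAMD-17", assessed at the end of treatment. Treatment lasts 8 weeks, so this is the same time point as response. The definition does not require a remitter to have improved by any amount, and patients already at or below a cut-off at baseline are not set aside.
- **Clinically important change (Primary Outcome):** the minimal clinically important difference on MADRS is cited as 1.6–1.9 points of change from baseline.

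The Statistical Analysis section tests secondary outcomes two-sided at 0.05. The −10% margin is attached only to the primary outcome, MADRS response.

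**The concern.** Remission is normally read as the more demanding result: the patient has not just improved but is now nearly free of symptoms. Here the MADRS cut-off equals the lowest score at which a patient can be enrolled. At the bottom of the entry range the rule therefore records remission where there has been no change, or a change smaller than the protocol's own benchmark for clinical relevance. The trial recruits mild-to-moderate depression, so the low end of the scale is part of the intended population.

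The word joining the two scales adds to this. If it creates a single either/or endpoint, a patient above the cut-off on one scale still counts if the other scale is low. If it means two scale-specific rates, the text does not say so.

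What is at stake is the meaning of one secondary outcome. Patients who count as successes almost regardless of treatment raise the rate in both arms and tend to dilute a difference between them. A remission rate close to, or above, the response rate could also be misread as an unusually strong result.

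**Working it through.** The plan gives no figure on this point to reproduce. The check sets three stated rules side by side.

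**Inputs**
- Admissible baseline MADRS *b*: at least 12 and below 30 (Participants). Taking total scores as whole numbers, this is 12, 13, …, 29, or 29 − 12 + 1 = 18 values.
- MADRS remission: week-8 score ≤ 12 (Secondary Outcomes, item b).
- MADRS response: week-8 score ≤ *b*/2 (Primary Outcome).
- Minimal clinically important difference: 1.6–1.9 points (Primary Outcome).

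**Formulas**
- Fall needed for remission = *b* − 12.
- Fall needed for response = *b*/2, rounded up to a whole point.

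**Examples**

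| Baseline | Fall for remission | Fall for response | Easier to reach |
|---|---|---|---|
| 12 | 0 (0%) | 6 | remission, already met |
| 13 | 1 (8%) | 7 | remission |
| 16 | 4 (25%) | 8 | remission |
| 20 | 8 (40%) | 10 | remission |
| 23 | 11 (48%) | 12 | remission |
| 24 | 12 (50%) | 12 | equal |
| 25 | 13 (52%) | 13 | equal |
| 26 | 14 (54%) | 13 | response |
| 29 | 17 (59%) | 15 | response |

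**Counts over all 18 scores**
- Remission needs the smaller fall at 12–23: 12 of 18 (67%). Leaving out 12 itself, 11 of 17 (65%).
- Equal at 24–25: 2 of 18.
- Remission needs the larger fall at 26–29: 4 of 18 (22%).
- MADRS remission already met at entry: 1 of 18, the score of 12.
- MADRS remission reachable with a fall below 1.6 points: 2 of 18, the scores of 12 (0 points) and 13 (1 point).

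**Consequence for nesting.** At every baseline from 12 to 25 (14 of 18 scores), half the baseline, rounded down, is at most 12. Every MADRS responder in that range is therefore also a MADRS remitter, and the remission rate there cannot be lower than the response rate.

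**Does a lower cut-off alone help?** Any cut-off of 11 or below removes the overlap with entry. The ordering remains: remission is still the smaller fall at 10 of 18 scores with a cut-off of 11, at 8 with 10 and at 6 with 9. These values only show sensitivity; none is proposed.

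**HAMD-17 route.** No entry range is stated for HAMD-17, so no count is possible. The stated criteria do not exclude a baseline of 7 or less. If the two scales form one either/or endpoint, this route can only add remitters. If they are two separate rates, the MADRS results above are unchanged.

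**The case against.** The strongest reply is that response and remission measure different things. Response is relative change and remission is an end state, and nothing in the article says that one must be nested in the other. Some crossing is to be expected whenever a fixed cut-off is set against a percentage rule, as the results for lower cut-offs show. This largely stands: the ordering by itself is not an error, and a remission rate above the response rate could still be read as the share of patients with low scores at week 8. It does not answer the overlap with entry. An end state that a patient may already occupy at enrolment does not show that anything was achieved.

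Three stronger readings are tempting, and the documents do not support them.

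- *A reader might infer that some patients do enter in remission.* The criteria only allow it, and on MADRS only at the single score of 12. The number could be close to zero. A HAMD-17 of 7 or less at entry is likewise only not excluded, and patients must also have a confirmed ICD-10 diagnosis and a MADRS of at least 12.
- *A reader might infer that remission is easier for most patients.* The 12 of 18 counts score values. If enrolment sits mainly in the upper 20s, remission would be as hard as response or harder for most patients.
- *A reader might infer that the non-inferiority conclusion is compromised, or that remission cannot separate the arms.* The margin and the one-sided test belong to MADRS response alone, and no non-inferiority claim is set for remission. Reduced sensitivity is plausible, but its size cannot be calculated from the article. Changes in MADRS and HAMD-17 and HAMD-17 response are reported as well.

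**Conclusion.** The concern holds for one secondary outcome. The entry criterion and the remission definition overlap, so a patient admitted at MADRS 12 counts as remitted unchanged, and one admitted at 13 does so with a fall below the protocol's cited threshold for clinical importance. Remission needs a smaller fall than response at 12 of the 18 admissible scores, an equal fall at 2 and a larger fall at 4. The either/or wording leaves open a second route that has no entry minimum.

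The conclusion rests on whole-number MADRS totals and on reading the end of treatment as week 8. How many patients are affected, and by how much the remission rates rise, is unknown without the baseline distribution. The remission rate may include patients with little or no improvement and be less able to tell the arms apart. The primary analysis and its non-inferiority test are unaffected. The definition should be corrected, but it does not threaten the trial's main conclusion.

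**What to change.** Reconcile the two sections by amending the outcome definition:

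1. Replace the either/or with two separate secondary outcomes, MADRS remission and HAMD-17 remission.
2. Count a patient as remitted on a scale only if the cut-off is met and there is also a reduction of at least 50% from baseline on that same scale.

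Lowering the MADRS cut-off to just below 12, without the second condition, would remove the overlap with entry but leave remission the easier target at 10 of 18 scores.

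The change takes about one sentence in Secondary Outcomes. Both scales are already collected at baseline and week 8, so data collection does not change, and the sample size is not touched. It should be made before outcome data are analysed, since a later redefinition would look data-driven.

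There are costs. Remission rates will be lower in both arms, and remission will no longer be purely an end-state measure. With the cut-off kept at 12, MADRS remission would also coincide with MADRS response for baselines 12–25, because a 50% fall from any of these already gives 12 or less. It would be stricter only at 26–29. The trial team should accept that knowingly. If the plain end-state proportion is still of interest, it can be reported descriptively, with the number of patients already at or below each cut-off at baseline.
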